### Ethics

The project involves clinical experimentation with human participants. The investigators adhere to the Helsinki Convention and the Madrid Declaration of the World Psychiatric Association on clinical research. The present project has been submitted for approval to the Ethics and Research Committee of the University of Valencia, and when we receive approval from this committee (UV-INV_ETICA-1623849), the document will form part of the final documentation of the present study. All participants will be volunteers and will give their informed consent to participate in the study. All eligible participants will be given oral and written information about the study and the two intervention modalities. Specifically, they will be informed that they may leave the study at any time, without providing any explanation, and that this decision will in no way affect their family member's regular treatment at the center. Participant selection and evaluation will be carried out by qualified personnel who will not know the condition to which a given participant has been assigned. In the same way, the treatments will be carried out by qualified and expert professionals. Furthermore, it should be emphasized that the protocols for action and custody of the information followed at the University Clinical Hospital, and the PREVI Clinical Center, , where the participants will be recruited and the interventions will be carried out, comply with all the requirements of the LOPD (Organic Law 15/1999, of 13 December 2018). In addition, according to the existing knowledge in this field so far, we have not found any risks for the participants; however, the appearance of any important clinical change that would involve any type of risk would not only imply removal of the participant from the project, but also his/her referral for specialized study and care. The assessment protocol described above is composed of standardized instruments that are risk-free for the participants (interviews, questionnaires, registers). The intervention protocols are based on empirically validated treatments (cognitive-behavioral oriented) designed and developed by staff with extensive knowledge and experience in this field. For ethical reasons, participants in the control condition, where the psychoeducation protocol (TAU-O) will be applied, will be given the opportunity to receive the FC-SDB program if they so desire, even if the study has already ended. The study was registered at clinicaltrials.gov as ID: NCT05157607

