### Procedure

Family members of patients with SBD will be given the opportunity to participate in the study. Once they have completed the informed consent, an expert clinician will carry out the assessment of each participant to check that the inclusion and exclusion criteria are met, and an independent investigator, unaware of the characteristics of the study, will be contacted to carry out randomization. At all times, for randomization purposes, an experimenter from outside the research team will assign each family member to one of the two study conditions (FC-SBD or TAU-O) using a random number software program. The randomization sequence will be concealed from the clinicians participating in the study. Independent assessors will administer the assessment protocol to the participants without being aware of the experimental condition to which they belong (FC-SBD or TAU-O). Patients will also be assessed before starting the intervention programs for relatives. After the assessment has been completed, all the relatives will start to receive the intervention in the condition to which they have been assigned. In the case of patients, they will participate in their current treatment or care. At the end of the intervention, the assessment protocol will be readministered to both relatives and patients, again by independent assessors, and the same thing will be done at the six-month follow-up.

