
### Interventions

#### Interventions with family members

##### Family Connections Protocol for Relatives of Patients with SBD (FC-SBD)

The intervention lasts three months and includes 12 sessions with a weekly two-hour group format.

The FC program [23] is divided into six modules:Module 1: Up-to-date information and research on suicide (Epidemiology, frequency, Risk factors, protective factors).Module 2: Psychoeducation on the development of suicide, explanatory theories, available treatments, comorbidity.Module 3: Emotional regulation skills, skills of acceptance, validation, approach, awareness, and to decrease emotional reactivity.Module 4: Skills to improve the quality of relationships in family interactions (letting go of guilt and anger, acceptance skills in relationships).Module 5: Communication skills and effective self-expression.Module 6: Problem management and making safe plans for crisis management.All the modules include practice exercises, video viewing, and homework assignments. In addition, throughout the program, with the aim of increasing social support, the FC-SBD program provides a forum where participants can stay in touch and share common problems and solutions.

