##### Treatment as Usual Optimized Protocol (TAU-O)

Family members in this condition will continue to receive their treatment as usual in their care center of reference. In addition, we will optimize the treatment based on the recommendations of the international guidelines for the treatment of suicide. There will be one three-hour session in group format with the following component:Module 1: Updated information and research on suicide (Epidemiology, frequency, Risk factors, protective factors). Psychoeducation on the development of Suicide, Explanatory theories. Available treatments, and comorbidity.

In both conditions, after each face-to-face session, the participant will be asked to review the contents covered during the session as homework (independently of the homework corresponding to the specific module being addressed). All interventions carried out with family members will be performed by clinical psychologists or general health psychologists with at least a Master's degree or a doctoral degree and previous training in the administration of the programs.

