#### Burden assessment scale [40]

This 19-item scale assesses two dimensions of caregiver burden of a loved one's illness (objective and subjective) in the past six months. The items are rated on a 4-point Likert scale (1-4), where higher scores indicate higher levels of illness burden. The psychometric properties of this scale are adequate, with an internal reliability between .89 and .91 and adequate validity [41].2. Measures of secondary outcomes

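### The safety rule in the Ethics section removes an at-risk relative from the whole study, so outcome assessments would stop along with the intervention

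*Protocol article*

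**What the plan says.** The Ethics section states that "any important clinical change that would involve any type of risk would not only imply removal of the participant from the project", and adds referral for specialised care. The Participants section defines the participants as the relatives. The Ethics section opens with "The project involves clinical experimentation with human participants", so the project there is the study as a whole.

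The same section says "we have not found any risks for the participants". The sentence after the removal rule reads: "The assessment protocol described above is composed of standardized instruments that are risk-free for the participants".

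Under Procedure, assessments are repeated at the end of the intervention, "and the same thing will be done at the six-month follow-up". Relatives who have been removed are not mentioned. Data analyses commits to intention to treat at post-treatment and six months, using mixed-effects models fitted by maximum likelihood.

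**The concern.** A safety rule should stop the treatment where necessary and get the person care. This one, as worded, also stops measurement. Three things make that undesirable.

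- **The trigger may be related to the outcome.** A clinically important change involving risk is plausibly correlated with burden, and probably more closely with the DASS-21, which covers the past week. The missing values are then not a random subset.
- **The analysis cannot repair it.** Likelihood-based estimation assumes that missingness is explained by what was observed. A relative who deteriorates between baseline and the post-treatment visit, and is then removed, contributes only a baseline score. The deterioration itself is unseen.
- **Detection may differ by arm.** FC-SBD "includes 12 sessions with a weekly two-hour group format". For TAU-O, "There will be one three-hour session in group format". Study staff have far more opportunity to notice a change in FC-SBD, so removal could be unbalanced even if the true risk were not.

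Intention to treat is weakened, not contradicted, because data collected before removal stay in the model. At stake is a small and avoidable loss of outcome data whose effect the trial could not check.

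**Working it through.** **Reading the text.** In the Ethics section, project denotes the study, and separate words are used for the treatments and interventions. The narrower term was available and was not used. No other section keeps removed relatives in the assessment schedule. Since that section calls the instruments risk-free, the safety reason does not by itself require the questionnaires to stop.

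**Size.** The plan gives no removal rate, so there is no figure of its own to reproduce on this point. What follows is an illustration.

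Inputs from the Sample size section: planned effect 0.60 SD for burden; 62 randomised and 45 evaluable per arm.

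Assumed inputs:
- Burden at baseline, post-treatment and six months is normal with SD 1 and a common correlation rho of 0.3, 0.5 or 0.7 between visits. The FC-SBD mean is 0.60 lower at both later visits.
- Risk trigger t = r × post-treatment burden + sqrt(1 − r²) × independent noise, with r = 0.3 or 0.5.
- One threshold for both arms, exceeded by 3% of TAU-O (0.03 × 62 = 1.9, about 2 relatives). The share exceeding it in FC-SBD is then 2.0% (r = 0.3) or 1.5% (r = 0.5), about 1 of 62.
- Removed relatives keep baseline only.

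Likelihood estimate of each arm mean = completer mean + pooled slope on baseline × (baseline mean of all − baseline mean of completers).

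*Hand check for r = 0.5, rho = 0.3, equal noticing.* Removing those above the threshold c lowers the completers' post-treatment mean by r × φ(c)/Φ(c). Adjusting for baseline leaves about (1 − rho²) = 0.91 of that.
- TAU-O: c = 1.881, so 0.5 × 0.0680/0.970 = 0.0351.
- FC-SBD: c = 1.881 + 0.5 × 0.60 = 2.181, so 0.5 × 0.0370/0.985 = 0.0188.
- Shift in the difference: 0.91 × (0.0351 − 0.0188) = 0.015, giving 0.585.
- Removal in FC-SBD only: 0.91 × 0.0188 = 0.017, giving 0.617.

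The simulation (3,000,000 relatives per arm, Monte Carlo error about 0.001 to 0.002) gives 0.586 and 0.618 for these two cases.

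*Simulated estimates over r = 0.3, 0.5 and all three rho unless stated; true value 0.600:*

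| Who is removed | Post-treatment | Six months |
|---|---|---|
| Noticed equally in both arms | 0.586 to 0.597 | 0.595 to 0.599 |
| Noticed fully in FC-SBD, half the time in TAU-O | 0.600 to 0.603 | 0.599 to 0.603 |
| Noticed in FC-SBD only | 0.608 to 0.618 | 0.601 to 0.605 |
| Found at the post-treatment visit, after scoring (r = 0.5) | 0.600 | 0.600 to 0.601 |
| More frequent: 3% of FC-SBD, 6% of TAU-O (r = 0.5) | 0.574 to 0.584 | 0.592 to 0.595 |

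*Cruder outer range.* If a share p of one arm and none of the other is removed, and those removed are k SD worse than the observed data predict, the difference shifts by p × k. This runs from 0.02 × 0.5 = 0.01 to 0.10 × 1.5 = 0.15 SD. The upper end needs 10% removal confined to one arm and a large unseen worsening. Nothing in the document points to that.

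**The case against.** The sentence is a safety statement whose purpose is referral, and it says nothing explicit about outcome collection. Procedure repeats the assessments without excluding anyone, and Data analyses promises intention to treat at those visits. How stopping treatment differs from leaving the study is detail that a condensed article often leaves to the full protocol. On the numbers, the effect is slight: with 45 per arm the standard error of a standardised difference is about sqrt(2/45) = 0.21, so a bias of 0.02 is about a tenth of a standard error. It is also small beside the planned 30% dropout. The direction is open, every driver is assumed, and no risks are expected. The primary scale measures burden of "illness (objective and subjective) in the past six months", so it is not a marker of acute risk. Finally, calling the instruments risk-free in general does not show that questioning a relative newly judged at risk is appropriate.

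Most of this stands as a limit on the size of the point, and it is why the point is minor. It does not remove the point. The article states a removal rule and words it to cover the study, so this is not silence left to a fuller document. The last objection is met by letting a clinician defer an assessment.

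**Conclusion.** The concern holds as a minor one. As written, the rule takes the relative out of the study, and nothing in the article restores the later assessments. The loss would be avoidable, possibly related to the outcome, and beyond what the mixed model can recover.

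Its size cannot be determined from the document. Under the base assumptions the bias in the burden effect is about 0.02 SD or less. It is towards zero if changes are noticed equally and away from zero if they are noticed only in FC-SBD. It is near zero if noticing is partly unbalanced or happens at the post-treatment visit after scoring. It grows only if removal is more frequent and closely follows the unrecorded score. Removal rate, trigger correlation, share noticed and between-visit correlation are all assumptions. Confidence is medium, because the authors may have meant removal from the intervention only.

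**What to change.** Keep the referral and reword the sentence. An important clinical change involving risk stops the study intervention and triggers referral. Post-treatment and six-month assessments continue for every randomised relative who agrees, deferred if the clinician judges it necessary. Record the date and reason for stopping, and analyse these relatives in their randomised arm.

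The cost is one sentence of protocol wording and a few extra questionnaires, with consent. If follow-up is already complete, report by arm how many relatives were removed under this rule, why, and whether they were assessed afterwards.

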
### Interventions

#### Interventions with family members

##### Family Connections Protocol for Relatives of Patients with SBD (FC-SBD)

The intervention lasts three months and includes 12 sessions with a weekly two-hour group format.

The FC program [23] is divided into six modules:Module 1: Up-to-date information and research on suicide (Epidemiology, frequency, Risk factors, protective factors).Module 2: Psychoeducation on the development of suicide, explanatory theories, available treatments, comorbidity.Module 3: Emotional regulation skills, skills of acceptance, validation, approach, awareness, and to decrease emotional reactivity.Module 4: Skills to improve the quality of relationships in family interactions (letting go of guilt and anger, acceptance skills in relationships).Module 5: Communication skills and effective self-expression.Module 6: Problem management and making safe plans for crisis management.All the modules include practice exercises, video viewing, and homework assignments. In addition, throughout the program, with the aim of increasing social support, the FC-SBD program provides a forum where participants can stay in touch and share common problems and solutions.

##### Treatment as Usual Optimized Protocol (TAU-O)

Family members in this condition will continue to receive their treatment as usual in their care center of reference. In addition, we will optimize the treatment based on the recommendations of the international guidelines for the treatment of suicide. There will be one three-hour session in group format with the following component:Module 1: Updated information and research on suicide (Epidemiology, frequency, Risk factors, protective factors). Psychoeducation on the development of Suicide, Explanatory theories. Available treatments, and comorbidity.

In both conditions, after each face-to-face session, the participant will be asked to review the contents covered during the session as homework (independently of the homework corresponding to the specific module being addressed). All interventions carried out with family members will be performed by clinical psychologists or general health psychologists with at least a Master's degree or a doctoral degree and previous training in the administration of the programs.

### Treatment of patients

With regard to the treatment of patients, the routine treatment they receive in their centers of reference will be followed. All interventions will be carried out by the clinical psychologists and psychiatrists working in these centers.

### Measures

After reviewing the literature, an evaluation protocol was designed that includes the main instruments that have been commonly used by authors working in this field [17, 23, 39], as well as some additional instruments that we consider relevant to the hypotheses proposed. In all cases, the Spanish validations of the assessment instruments will be used; if they do not exist, the validations will be carried out by the researchers of this study.

### Measures - Relatives (participants)

**Data on demographic variables**: age, sex, educational level, income, marital status, number/age of children, and history of psychological treatment.1. Measures of primary outcomes

#### Burden assessment scale [40]

This 19-item scale assesses two dimensions of caregiver burden of a loved one's illness (objective and subjective) in the past six months. The items are rated on a 4-point Likert scale (1-4), where higher scores indicate higher levels of illness burden. The psychometric properties of this scale are adequate, with an internal reliability between .89 and .91 and adequate validity [41].2. Measures of secondary outcomes

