**Methods:**

The study design consists of a two-arm randomized controlled trial with two conditions: FC-SBD or Treatment as usual optimized (TAU-O). Participants will be relatives of patients who meet DSM-5 criteria for SBD. The caregivers` primary outcome measures will be the BAS. Secondary outcomes will be DASS-21, FES, DERS, QoL. The patient’s primary outcome measures will be the frequency of critical incidents with the family member with SBD. Secondary measures will be the INQ, PHQ-9, OASIS. Participants will be assessed at pretreatment, post-treatment, and 6-month follow-up. The intention-to-treat principle will be used when analyzing the data.

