### Methods and design

#### Study design

This study is a superiority trial. The study design consists of a two-arm randomized controlled trial (RCT). On the one hand, there will be two conditions: Family Connections (FC-SBD) or Treatment as usual optimized (TAU-O), and family members will be randomized to one of the two groups. Family members will be randomized taking into account that if a patient has more than one family member attending the group, they will be randomized together to be included in the same condition. The effects of the treatment will be measured before starting the group, afterwards, and at the six-month follow-up in order to know whether the effects are maintained in the long term. Figure 1 shows the flow chart. This protocol will follow the CONSORT statement (Consolidated Standards of Reporting Trials, http://www.consort-statement.org) [30, 31] and the SPIRIT guidelines (Standard Protocol Items: Recommendations for Interventional Trials) [32, 33].

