##### Register of critical incidents with the family member with SBD

This register was developed ad hoc for this study. The questions recorded are the following: frequency of suicide attempts in the past six months, number of days of self-harm in the past six months, number of episodes of verbal/physical violence with caregivers in the past six months; frequency of visits to the psychiatric emergency room in the past six months, frequency of therapy sessions conducted out of schedule in the past six months (face-to-face, phone calls, etc.).

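### Both primary measures use a six-month recall window but are first repeated after a three-month programme, so about half of the post-treatment window lies before treatment

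*Protocol article*

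**What the plan says.** - **BAS.** The Burden assessment scale section of the protocol article gives the recall period as "illness (objective and subjective) in the past six months". It is the only primary outcome for relatives.
- **Register.** The critical-incident section attaches the same period to all five items, for example "frequency of suicide attempts in the past six months, number of days of self-harm in the past six months". The abstract's Methods paragraph says "The patient’s primary outcome measures will be the frequency of critical incidents with the family member with SBD". For relatives the register is a secondary outcome. The study team built the form for this trial.
- **Programme length.** "The intervention lasts three months and includes 12 sessions with a weekly two-hour group format". For TAU-O, "There will be one three-hour session in group format with the following component".
- **Visits.** "Participants will be assessed at pretreatment, post-treatment, and 6-month follow-up". The Procedure section places the second assessment at the end of the intervention.
- **Sizing.** The Sample size section plans for d = 0.60 on burden, two-sided alpha 0.05 and power 0.80, which gives 45 relatives per condition.

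The article mentions no shorter recall period after baseline and no handling of overlapping windows.

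**The concern.** A six-month look-back taken three months after the programme starts reaches three months behind the start. Burden and incidents from that stretch cannot have been changed by the programme, and the baseline assessment has already covered them. Under randomisation this shared stretch is expected to be alike in the two arms, so it pulls the between-arm difference at post-treatment toward zero. It does not favour FC-SBD or raise the false-positive rate. What is at stake is a real benefit being missed or understated at the first visit after treatment.

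A second effect concerns the follow-up. If recall averages over the window, a constant true effect would look small at post-treatment and larger at six months. That could be mistaken for delayed benefit when the plan asks whether effects are maintained.

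**Working it through.** **1. The plan's own figure.** A two-sample t-test with d = 0.60, two-sided alpha 0.05 and power 0.80 needs 44.6 per arm, rounded up to 45. Power at 45 per arm is 0.804. The stated 90 evaluable relatives are reproduced.

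**2. Share of the post-treatment window before treatment.** Inputs are the six-month recall (about 26 weeks, or 182.6 days) and the programme length. Share = 1 − (time since start ÷ window).

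| Time from first session to assessment | Share before treatment |
|---|---|
| 3 months, as stated | 1 − 3/6 = 50% |
| 12 weeks (84 days) | 1 − 84/182.6 = 54% |
| 11 weeks, first to last session (77 days) | 1 − 77/182.6 = 58% |
| 12 weeks plus a 2-week delay (98 days; the delay is assumed) | 1 − 98/182.6 = 46% |

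The overlap with the baseline window is about three months.

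**3. Register counts.** Assume a steady incident rate that is equal in both arms before treatment, no change in the control arm, and a true halving from day 1. Observed ratio = (time before + 0.5 × time on treatment) ÷ window.
- Three months: (3 + 0.5 × 3)/6 = 0.75.
- Twelve weeks: (14 + 0.5 × 12)/26 = 0.77.

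A true ratio of 0.50 is thus recorded as 0.75 to 0.77. If the effect builds up over the sessions, the recorded ratio is closer still to 1.

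**4. BAS.** The article does not say how respondents weight the window, so the weight *w* on the treatment period is an assumption. Observed d = 0.60 × *w*, with the SD unchanged and 45 per arm.

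| *w* | Observed d | Power | Per arm for 0.80 power |
|---|---|---|---|
| 0.46 (proportional, 12 weeks) | 0.28 | 0.25 | 208 |
| 0.50 (proportional, 3 months) | 0.30 | 0.29 | 176 |
| 0.75 (leaning to recent weeks) | 0.45 | 0.56 | 79 |
| 1.00 (treatment period only) | 0.60 | 0.80 | 45 |

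**5. Use of baseline.** The Data analyses section plans repeated-measures and mixed-effects models. With adjustment for baseline the effective d is d/√(1 − r²). At d = 0.277 and an assumed pre-post correlation of 0.5, this is 0.277/0.866 = 0.32, with power about 0.32. At an assumed correlation of 0.7 it is 0.277/0.714 = 0.39, with power about 0.44.

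**6. Follow-up.** Counted from the end of treatment, a six-month window at a six-month visit lies wholly after the programme and holds no pre-treatment time.

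**The case against.** Several points against the concern stand.

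- **The BAS is a rating, not a count.** Respondents may answer from how things have been lately. Step 4 includes the case of no loss, so dilution of the BAS is plausible but not demonstrated.
- **The planned 0.60 may already be diluted.** It was chosen from effects observed in earlier family-intervention studies, including 0.45 for burden. If their scales used a similar look-back, multiplying by 0.46 or 0.50 discounts twice. The article does not say which scales they used, so this can be neither confirmed nor ruled out.
- **The sizing concerns burden only.** No stated sample size rests on the register, so the power figures do not apply to the outcome where dilution is close to arithmetic.
- **A clean visit is already planned** and will be analysed.

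Stronger readings are tempting but not supported:

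- *More than half of the window precedes treatment.* The stated three months give exactly half. The 54% and 58% figures need a count in weeks and an immediate assessment, and a two-week delay brings the share below half.
- *The trial's power is 0.25.* That holds only under time-proportional recall, an undiluted 0.60 and a test that ignores baseline.
- *The diluted visit is the primary test.* Hypothesis (a) speaks of change after the intervention, which may suggest this. But the article names no primary time point, and a condensed article may leave that to the full protocol.
- *Control relatives are reassessed straight after their single session*, so nearly all of their window precedes treatment. The article does not spell out their assessment date, so this cannot be concluded.

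None of this removes the mismatch between the recall window and the visit schedule, which the article itself fixes.

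**Conclusion.** The concern holds in a limited form. At post-treatment, about half of the recall window of both primary measures lies before treatment and repeats time already covered at baseline.

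For the register, given steady rates and accurate counting, this turns a true halving into a ratio of about 0.75 to 0.77. That biases the patients' primary outcome toward no effect at that visit. For the BAS the direction is the same but the size is unknown: power at 45 per arm could be anywhere from about 0.25 to 0.29 up to 0.80. Less is lost if the planned effect already reflects a similar window or if baseline is used in the model. The six-month follow-up is not affected if it is counted from the end of treatment.

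This should be fixed, with moderate confidence. The register is the firmer ground.

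**What to change.** **Register.** After baseline, ask about incidents *since the last assessment*. Where the six-month form is already in use, add a count since the start of the programme. Analyse the counts as rates, with observation time as an offset.

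**BAS.** Keep the validated wording. Define follow-up as at least six months after the end of the 12-week period. State in advance that the post-treatment contrast is expected to be diluted and that the follow-up contrast is the one with a clean window.

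**Optional.** Naming follow-up as the primary time point for the BAS would put the main test on the clean window, but it is a trade-off. Dropout may be higher by then. The Ethics section also offers control relatives FC-SBD without stating that they wait until follow-up is complete, so crossover is possible. If this option is taken, fix it before outcome data are seen.

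**Cost.** A small edit to the study's own form and some protocol wording. Because the Participants section describes the study as ongoing, record the form version for each assessment so that the two recall windows are not pooled unknowingly.
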